## Abstract

**Background:**

The COVID-19 pandemic has placed health care workers (HCWs) under severe stress, compounded by barriers to seeking mental health support among HCWs. The Essential Network (TEN) is a blend of digital and person-to-person (blended care) mental health support services for HCWs, funded by the Australian Federal Department of Health as part of their national COVID-19 response strategy. TEN is designed as both a preventative measure and treatment for common mental health problems faced by HCWs. New blended services need to demonstrate improvements in mental health symptoms and test acceptability in their target audience, as well as review implementation strategies to improve engagement.

**Objective:**

The primary objective of this implementation study is to design and test an implementation strategy to improve uptake of TEN. The secondary objectives are examining the acceptability of TEN among HCWs, changes in mental health outcomes associated with the use of TEN, and reductions in mental health stigma among HCWs following the use of TEN.

**Methods:**

The implementation study contains 3 components: (1) a consultation study with up to 39 stakeholders or researchers with implementation experience to design an implementation strategy, (1) a longitudinal observational study of at least 105 HCWs to examine the acceptability of TEN and the effectiveness of TEN at 1 and 6 months in improving mental health (as assessed by the Distress Questionnaire [DQ-5], Patient Health Questionnaire [PHQ-9], Generalized Anxiety Disorder [GAD-7], Oldenburg Burnout Inventory [OBI-16], and Work and Social Adjustment Scale [WSAS]) and reducing mental health stigma (the Endorsed and Anticipated Stigma Inventory [EASI]), and (3) an implementation study where TEN service uptake analytics will be examined for 3 months before and after the introduction of the implementation strategy.

**Results:**

The implementation strategy, designed with input from the consultation and observational studies, is expected to lead to an increased number of unique visits to the TEN website in the 3 months following the introduction of the implementation strategy. The observational study is expected to observe high service acceptability. Moderate improvements to general mental health (DQ-5, WSAS) and a reduction in workplace- and treatment-related mental health stigma (EASI) between the baseline and 1-month time points are expected.

**Conclusions:**

TEN is a first-of-a-kind blended mental health service available to Australian HCWs. The results of this project have the potential to inform the implementation and development of blended care mental health services, as well as how such services can be effectively implemented during a crisis.

**International Registered Report Identifier (IRRID):**

DERR1-10.2196/34601

## Introduction

### Background

The stress of the COVID-19 pandemic is placing health care workers (HCWs) at increased risk of poor mental health [1], with posttraumatic stress disorder (PTSD) being a major concern [2-5]. Mental health treatments can lower the risk of HCWs developing mental ill-health [1], yet few appropriate services are available at the necessary scale for all specializations of HCWs. The Australian health care workforce is currently estimated at 800,000 [6]. This figure will likely continue to grow alongside population growth, indicating that large-scale solutions are required. Early in the COVID-19 pandemic, researchers called for evidence-based, self-guided mental health services for HCWs, citing reluctance to seek help, coupled with the challenges of delivering quality support to thousands of time-poor consumers [7]. Blended care services that integrate digital (websites and apps) and person-to-person (including telehealth) services [8] can rapidly scale, while offering a personalized choice of evidence-based care options [9]. In this manner, blended care is a promising means of providing large-scale mental health services to HCWs during the ongoing COVID-19 pandemic.

Over and above scalability, mental health services must be sensitive to the specialized needs of HCWs. As HCWs battle the pandemic, they face numerous sources of stress, such as fear of infection [10], unsupportive workplaces [11], and even watching colleagues die [12]. HCWs also vary in how they manage these stressors across time [13]. Therefore, HCWs need adaptable mental health services that can help with a range of concerns, from situational distress to moral injury [14] to PTSD [2,3]. Yet, even services tailored to HCWs have seen little uptake despite high reported demand [15]. One likely explanation is the lack of psychological safety many HCWs experience when accessing mental health care. Concerns about stigma [1,16], confidentiality, and discrimination from colleagues or employers [17,18] keep many HCWs from using the available services. Blended care can address some of these concerns through digital services (eg, anonymous chat-based therapies, accessing tailored resources without registration), while still providing the flexibility for HCWs who prefer person-to-person care to access these services.

To fully leverage the potential of blended care to support HCWs during the COVID-19 pandemic and beyond, services must be implemented in a way that ensures HCWs feel psychologically safe to use them. Thus far, little is known about implementing these services is a way that builds trust and increases uptake of available services. The few studies within the COVID era describe institution-specific implementation practices without data on the effectiveness of implementation strategies [19]. Studies implementing HCW-specific mental health services from previous pandemics are largely of poor quality and evaluate the effects of an intervention rather than implementation strategies to facilitate uptake and engagement [20]. These challenges exemplify implementation science in digital health, which is yet to produce a unified implementation framework to guide not only the reporting of strategies but also the evaluation of certain approaches [21,22]. Understanding how to effectively implement HCW-specific mental health services could boost the uptake of available care and inform the development of new services as the pandemic continues to unfold.

### The Essential Network

The Essential Network (TEN) was funded by the Australian Government Department of Health as part of its national COVID-19 response strategy. TEN follows a sequential blended care approach [9] using an integrated service model that spans 4 care phases: (1) well-being promotion, (2) early detection and preventative interventions, (3) low-to-moderate-intensity services for HCWs experiencing preclinical distress, and (4) person-to-person clinical services for HCWs’ mental health difficulties or clinical distress. In this sequential blended care approach, users engage with digital resources and treatment options, as required, and progress to person-to-person clinical services, where necessary. This selection of treatment options is made possible by a “digital ecosystem” that brought together a network of existing and new services from partner organizations with interest in the mental health of HCWs. Services are made available through a single web-based digital hub (Figure 1) accessible across desktop, laptop, and mobile web browsers. Digital services comprise an online mental health assessment, mental health resources and advice for assisting individuals and their colleagues, and links to other relevant resources and organizations (eg, psychiatrists who treat HCWs, peer support organizations). Person-to-person services comprise up to 5 individual clinical consultations with either a clinical psychologist or a psychiatrist delivered either via telehealth or in person at our clinic in Sydney, New South Wales (NSW), Australia. Users can select and explore the digital or person-to-person options that they believe best match their needs.

**Figure 1 figure1:**
[figure not shown]
Example screenshots from the TEN website: home page (left), an online mental health assessment tool (top right), and evidence-based tools for practical self-help (bottom right). TEN: The Essential Network.

### Implementation Framework

This study will examine the implementation of TEN, a blended mental health service for Australian HCWs established during COVID-19, funded by the Australian Federal Government. The Consolidated Framework for Implementation Research (CFIR) framework will be used to guide this examination as the constructs within the CFIR span both implementation and effectiveness within a health service context [23]. However, some adaptation of the CFIR will be required. The CFIR assumes that an intervention will be implemented in a single organization or industry, unlike TEN, which spans many organizational structures and professions. Similarly, the frameworks consolidated within the CFIR are largely aimed at implementing singular, intervention-based face-to-face services, rather than multichannel digital services like TEN. Previous attempts to consolidate implementation strategies for digital mental health have focused on delivering specific digital programs as an alternative to traditional mental health services, rather than linking users to a range of care options in the way TEN does [21]. Work is underway to consolidate optimal digital health implementation strategies [22]; however, no such framework exists yet. For these reasons, in our study, the CFIR subconstruct definitions described by Damschroder et al [23] will be adapted to the digital and multiorganizational nature of TEN, guided by the digital-specific implementation strategies suggested by Graham et al [21] (see Table 1).

### Study Objectives

The primary objective of this study is to work with HCW researchers, industry partners, and active TEN users to design and test an implementation strategy for TEN. The secondary objectives are to examine the acceptability of TEN, to measure any changes in psychosocial well-being associated with the use of TEN, and to determine whether TEN reduces mental health stigma among HCWs.

**Table 1 table1:** CFIR^a^ constructs and example interview questions.

CFIR subconstruct		Example interview question
**Intervention characteristics**		
	Intervention source	N/A^b^. TEN^c^ was externally developed.
	Evidence strength and quality	Interviews: Questions regarding perceptions of the quality of the TEN website/offering and beliefs that the care options offered will benefit the mental health of HCWs^d^.
	Relative advantage	Interviews: Questions regarding awareness of TEN equivalents and perceived advantages of TEN.
	Adaptability	Interviews: Questions regarding the capacity for TEN to be adapted to the needs of professional^e^ groups.
	Trialability	Interviews: Questions regarding the feasibility of implementation and the evaluation of TEN within a single organization or professional groups^e^.
	Complexity	Interviews: Questions regarding difficulty of implementing TEN.
	Design quality and packaging	Interviews: Questions regarding perception of the quality of TEN presentation to organizations and users^e^.
	Cost	Interviews: Questions regarding resourcing (financial, personnel, etc) and opportunity costs of using TEN.
**Outer setting**		
	Patient needs and resources	Interviews: Questions regarding knowledge of member/employee needs^e^ and how these align with the organizational strategy.
	Cosmopolitanism	Interviews: Questions regarding organizational networks.
	Peer pressure	Interviews: Questions regarding knowledge of related organizational efforts and how these might affect the organizational endorsement of TEN.
	External policies and incentives	Interviews: Questions regarding external policy considerations and how these might affect the organizational endorsement of TEN.
**Inner setting**		
	Structural characteristics	Interviews: Questions regarding the social architecture, age, maturity, and size of an organization and profession^e^.
	Networks and communications	Interviews: Questions regarding how organizations communicate with members or employees (generally and in relation to mental health).
	Culture	Interviews: Questions regarding norms, values, and basic assumptions of an organization and profession^e^.
	Implementation climate^f^	Interviews: Questions regarding current endorsement of TEN and whether TEN competes with other initiates for resources or strategic importance.
	Readiness for implementation^f^	Interviews: Questions regarding readiness of an organization to assist with the implementation strategy^e^.
**Characteristics of individuals**		
	Knowledge and beliefs about the intervention	Interviews: Questions regarding the value and knowledge of both TEN and digital/blended mental health^e^.
	Self-efficacy	Interviews: Questions regarding the capabilities of both stakeholders and members/employees^e^ to execute implementation strategies.
	Individual stage of change	Interviews: Questions regarding the stage of change most members/employees^e^ are likely in with respect to using TEN or blended mental health services^e^.
	Individual identification with organization	Interviews: Questions regarding how stakeholders perceive the relationship between their organization and members/employees^e^.
	Other personal attributes	Interviews: Questions regarding what personal traits, such as tolerance of ambiguity, intellectual ability, motivation, values, competence, capacity, and learning styles, of their members/employees^e^ are likely to affect the implementation of TEN.

^a^CFIR: Consolidated Framework for Implementation Research.

^b^N/A: not applicable.

^c^TEN: The Essential Network.

^d^HCW: health care worker.

^e^Language adapted to the multiorganizational context of TEN.

^f^Adaptation of original CFIR definitions to TEN.

## Methods

### Study Design

This study will follow an implementation-effectiveness hybrid design [24]. The protocol has 3 components (Figure 2). The *consultation study* component (Study 1) is a series of semistructured qualitative interviews conducted with stakeholders to explore the needs of Australian HCWs and develop an implementation strategy for TEN. The *observational study* component (Study 2) is a pre-/postobservational study with Australian HCWs evaluating the acceptability TEN, providing feedback on the implementation strategy, and examining any changes in mental health outcomes that are associated with use of the service. The *implementation study* (Study 3) component will be a pre-/postaudit of TEN users both before and after the implementation strategy is implemented [25].

**Figure 2 figure2:**
[figure not shown]
Flowchart depicting the design and components of the implementation trial. HCW: health care worker.

### Study Setting

There is no specific study site. Semistructured interviews carried out as part of the consultations will be conducted online via videocalls (eg, Zoom, Microsoft Teams). As a digital mental health hub, participants in the observational study will be able to participate in the study and access the TEN service from any location in Australia. If applicable, face-to-face consultations through the TEN Clinic may be conducted at the Black Dog Institute, [name], or via telehealth.

### Study 1: Consultation Study

#### Ethics

The consultation component received approval from the UNSW Human Research Ethics Panel (HC no. 3500) on June 7, 2021.

#### Participants

Participants in the consultation study will be representatives from Australian professional organizations (*n*=15-18) relevant to mental health or HCWs as well as researchers or staff from the Black Dog Institute (*n*=10-21) working on projects relevant to HCWs’ mental health.

#### Recruitment

Participants for the consultation component will be approached directly to discuss participation or emailed an invitation to the study and provided with an online participant information statement and consent form.

#### Data Collection

Qualitative data will be captured in semistructured interviews with HCW researchers and industry partners who represent the interests and views of their respective disciplines. Interview questions will be structured to elicit information directly relevant to the key constructs constituting the CFIR and derived from the subconstruct descriptions provided by Damschroder et al [23]. Where appropriate, questions regarding some CFIR subconstructs will be adapted to a multiorganizational or digital context.

### Study 2: Observational Study

#### Ethics

The observational component received approval from the UNSW Human Research Ethics Committee (HC no. 210394) on July 22, 2021.

#### Participants

Participants in the observational study will be self-identified Australian HCWs who currently reside in Australia and have sufficient English proficiency to participate. Participant status as HCWs will be verified using the Australian Health Practitioner Regulation Agency’s register of practitioners. Participants who cannot be verified using the register of practitioners will be contacted on a case-by-case basis to confirm eligibility.

#### Recruitment

Participants for the observational study will be recruited through advertisements on social media, emails sent to health professionals on an internal Black Dog Institute mailing list, emails from TEN partner organizations, and information about the study on the Black Dog Institute and TEN websites. Prospective participants who engage with advertisements or study details on the TEN website will be redirected to the online participant information statement and consent form. Participants who elect not to participate in the study will be provided with a link to TEN and informed they may use the service freely and anonymously.

#### Data Collection

Quantitative data will be collected through an observational study with Australian HCWs (Figure 3). Participants will provide online consent using the e-Consent feature of REDCap (Vanderbilt University). People who decline to participate will be provided with a link to TEN and asked to complete a brief survey asking why they opted not to participate.

**Figure 3 figure3:**
[figure not shown]
Flowchart depicting a progression through the observational study. DQ-5: Distress Questionnaire; EASI: Endorsed and Anticipated Stigma Inventory; GAD-7: Generalized Anxiety Disorder; OBI-16: Oldenburg Burnout Inventory; PCL-5: Posttraumatic Stress Disorder Checklist; PHQ-9: Patient Health Questionnaire; SAS CI 360: SAS Customer Intelligence 360; TEN: The Essential Network; WSAS: Work and Social Adjustment Scale.

After consenting, participants will provide information on demographics and mental health (Table 2), service acceptability (Table 3), and complete baseline mental health and stigma outcomes (Table 4). Mental health outcomes are identical to the TEN online assessment. To avoid the participants needing to repeat the online assessment on the TEN website after completing the baseline mental health outcomes, the survey baseline will provide the same assessment feedback. Participants will then be provided with a link to the TEN website and asked to engage with the service naturalistically for 6 months. The link provided to each participant is unique and associated with their consent record number. User engagement (eg, pages viewed) with the TEN website is recorded automatically through the SAS Customer Intelligence 360 (SAS CI 360) platform. SAS CI 360 is a commercial website analytics package that records website use. Using unique TEN website links sent to participants, their TEN website use will be extracted and linked to their other study data. Participants will be recommended to bookmark this link, and their unique link will be provided to them by email at baseline and after the 1-month follow-up.

**Table 2 table2:** Questions examining demographic and baseline mental health.

Baseline question	Time point	Classification	Type of question
Gender	Baseline	Demographics	Single selection
Age	Baseline	Demographics	Single selection
Where are you located?	Baseline	Demographics	Single selection
What best describes your profession?	Baseline	Demographics	Single selection
Have you previously used the TEN^a^ service?	Baseline	Mental health	Yes/no
COVID-19 has affected your mental health.	Baseline	Mental health	Likert scale
Have you ever seen a doctor, counsellor, or other health professional about your mental health?	Baseline	Mental health	Yes/no
If you were seeking help for a mental health problem, what type of service would you most likely choose?	Baseline	Mental health	Multiple selection
Which of the following were the most important reasons why you chose to participate in this study?	Baseline	Mental health	Multiple selection
Which parts of TEN are you most interested in?	Baseline	Mental health	Multiple selection
What is your current employment status as an HCW^b^?	6 months	Employment	Single selection

^a^TEN: The Essential Network.

^b^HCW: health care worker.

**Table 3 table3:** Questions examining TEN^a^ service acceptability.

Service acceptability question	Time point	Type of question
If you were seeking help for a mental health problem, what type of service would you most likely choose?	Baseline	Multiple selection
Which of the following were the most important reasons why you chose to participate in this study?	Baseline	Multiple selection
Which parts of TEN are you most interested in?	Baseline	Multiple selection
If you needed to, would you use the TEN Clinic if there was a service charge?	1 month	Yes/no
If you needed to, would you use the TEN Clinic if it was provided under Medicare?	1 month	Yes/no
TEN met my mental health and well-being needs.	1 month	Likert scale
TEN improved my awareness of my mental health.	1 month	Likert scale
TEN improved my psychological coping skills.	1 month	Likert scale
A mental health service I found through TEN improved my psychological coping skills.	1 month	Likert scale
I would recommend TEN to a colleague.	1 month	Likert scale
Which parts of TEN were most useful to you?	1 month	Multiple selection
Why did you find these parts of TEN useful?	1 month	Free text
Did TEN make it easier for you to find the mental health support you wanted?	1 month	Yes/no
Did TEN help you learn about new sources of support?	1 month	Yes/no
Did you have any other feedback about TEN?	1 month	Free text

^a^TEN: The Essential Network.

**Table 4 table4:** Mental health and psychosocial instruments.

Questionnaire	Outcome
DQ-5^a^	Psychological distress
PHQ-9^b^	Depression
GAD-7^c^	Anxiety
PCL-5^d^	PTSD^e^
OBI-16^f^	Burnout
WSAS^g^	Social- and work-related impairment
EASI^h^	Mental health stigma

^a^DQ-5: Distress Questionnaire.

^b^PHQ-9: Patient Health Questionnaire.

^c^GAD-7: Generalized Anxiety Disorder.

^d^PCL-5: Posttraumatic Stress Disorder Checklist.

^e^PTSD: posttraumatic stress disorder.

^f^OBI-16: Oldenburg Burnout Inventory.

^g^WSAS: Work and Social Adjustment Scale.

^h^EASI: Endorsed and Anticipated Stigma Inventory.

After using TEN for 1 month, participants will be provided with a survey containing service acceptability (Table 3), mental health and stigma outcomes (Table 4), feedback on the implementation strategy (Table 5), and self-reported service engagement (Table 5). After completing the survey, participants will be informed that their TEN website usage will be monitored for a further 5 months to examine persistence with the service. After 6 months, participants will be provided with a follow-up survey about employment (Table 2) and mental health outcomes (Table 4).

**Table 5 table5:** Questions examining the implementation strategy and service engagement.

Question		Type of question

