#### TEN Service Engagement

Engagement with TEN will be examined through survey questions provided to participants at the 1-month time point, as well as through website and service analytics. The questions will examine self-reported usage of TEN (Table 5). Website user analytics are automatically collected through the SAS CI 360 platform whenever a user interacts with the TEN website. These user analytics include the IP address of the user as well as which pages or resources were accessed and when. User analytics will be linked to the participant using the IP address provided during consent. TEN Clinic clinicians will also provide data from person-to-person clinical services, including whether a participant accessed the TEN Clinic and the number of sessions.

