### Study 2: Observational Study

#### Data Analysis

Descriptive statistics will be used to report the overall acceptability of TEN. The results from the observational study will be analyzed using linear mixed models to examine changes in reported psychosocial benefits over time (ie, baseline, 1 month). Patterns of service engagement and baseline outcome severity will be classified using cluster analyses or latent class analyses. These patterns will be used to examine how service engagement influences outcomes, as well as stratify participants baseline outcomes for subset analysis. Kaplan-Meier curves with TEN engagement data will be used to examine persistence with TEN over the course of the 6-month follow-up (ie, when participants ceased accessing the service). Missing data will be addressed using maximum likelihood estimation. This will answer the research questions by examining the acceptability of TEN among HCWs, patterns of service usage over time, any benefits observed after engaging with the TEN service, and persistence with the service over time.

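### Persistence is defined on the whole TEN service, but the only dated data named for months 1 to 6 are website visits; the Clinic data named carry no dates

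*Protocol article*

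**What the plan says.** Four parts of the protocol article bear on this.

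- **The service** (Introduction, The Essential Network). TEN is sequential blended care. Users start with digital resources and "progress to person-to-person clinical services, where necessary". The Clinic part is limited in length: "Person-to-person services comprise up to 5 individual clinical consultations with either a clinical psychologist or a psychiatrist".
- **What is monitored after month 1** (Study 2, Data Collection). After the 1-month survey, "participants will be informed that their TEN website usage will be monitored for a further 5 months to examine persistence with the service". The 6-month survey is described as covering employment and mental health outcomes.
- **What engagement data comprise** (Study 2, TEN Service Engagement). This section opens by naming its sources: "Engagement with TEN will be examined through survey questions provided to participants at the 1-month time point, as well as through website and service analytics". Website analytics are said to record what was accessed and the time of access. Clinicians supply Clinic data, "including whether a participant accessed the TEN Clinic and the number of sessions".
- **The analysis** (Study 2, Data Analysis). "Kaplan-Meier curves with TEN engagement data will be used to examine persistence with TEN over the course of the 6-month follow-up", with the event explained as "when participants ceased accessing the service". Persistence over time is listed there among the questions that the analysis is to answer.

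**The concern.** The quantity to be estimated is persistence with a service that has two parts, digital and person-to-person. The source tied to it in Data Collection covers only the digital part. Moving from one part to the other is a pathway the service intends, so a participant can stop visiting the website while still receiving TEN care.

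A Kaplan-Meier curve needs a date for each event. If the only dated contacts are website visits, a participant who has moved wholly to the Clinic looks the same on the curve as one who has abandoned TEN. A curve titled as persistence with TEN would then show persistence with the website, and would make the blended service look less well retained than it is. If dates are not obtained from the Clinic, no later analysis rule can put those contacts on the time axis.

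**Working it through.** The plan states no persistence figure, so there is nothing to reproduce. The check sets the named sources side by side, followed by an illustration of size.

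**1. Which named sources can date a contact after month 1?**

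| Source | Where described | Covers months 1 to 6? | Dated? |
|---|---|---|---|
| Website analytics | Data Collection; TEN Service Engagement | Yes | Yes, time of access is recorded |
| Self-reported use | Table 5; TEN Service Engagement | No, asked at 1 month about that month | No |
| 6-month survey | Data Collection | No engagement item described | No |
| Clinic data | TEN Service Engagement | Not stated | Access and session count named; no date named |

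As written, website analytics are the only dated source for the period over which persistence is to be read.

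**2. Direction.** Let W be a participant's last website access and C the last Clinic session. With both sources, the last contact is max(W, C). With the website alone it is W. Since max(W, C) is never earlier than W, leaving out Clinic sessions can only move cessation earlier. The same holds for a rule based on a gap without contact, because adding contacts can only postpone the gap.

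**3. Size, by assumption.** Let P be true persistence at 6 months and c the share of persisters who by then use only the Clinic. Assume complete follow-up. Website-only measurement gives

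observed persistence = P × (1 − c), with N × P × c participants misclassified.

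Neither P nor c is in the documents. N = 105 is the minimum sample from Study 2, Sample Size, used here only to convert shares to counts.

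| P (assumed) | c (assumed) | Observed P × (1 − c) | Misclassified, 105 × P × c |
|---|---|---|---|
| 50% | 5% | 47.5% | 2.625 |
| 50% | 10% | 45% | 5.25 |
| 50% | 20% | 40% | 10.5 |
| 50% | 40% | 30% | 21 |
| 30% | 5% | 28.5% | 1.575 |
| 30% | 10% | 27% | 3.15 |
| 30% | 20% | 24% | 6.3 |
| 30% | 40% | 18% | 12.6 |

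The shortfall is P × c: for example 0.50 × 0.05 = 2.5 percentage points and 0.50 × 0.20 = 10 percentage points. It is small when few participants are Clinic-only. How many weeks too early cessation would be dated cannot be stated, because the spacing of Clinic sessions is not given.

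**The case against.** The best defence is that the article does not restrict the analysis to the website. Data Analysis speaks of TEN engagement data and of access to the service, and TEN Service Engagement puts service analytics and clinician-supplied data under engagement. The sentence in Data Collection reports what participants will be told and is not an endpoint definition. The Clinic items are introduced as examples, so dates may be among the fields supplied. The exact cessation rule could properly sit in a fuller document. TEN is reached through a single web hub, so Clinic users may go on visiting the site. The Conclusion expects many health care workers to avoid person-to-person care, which would keep c small. Persistence is also descriptive: it is not named among the study objectives and does not drive the sample size.

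Most of this stands, and it limits what can be claimed. A reader might infer that the plan counts every participant who moves to the Clinic as having stopped. No section states such a rule. A reader might also infer that persistence would be biased by baseline severity. The plan stratifies by baseline outcomes for subset analysis but specifies no comparison of persistence across those strata, so that inference is not supported. Nor do the documents support a fixed figure for the understatement.

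The defence does not remove the mismatch. One section ties persistence with the service to website monitoring, another defines the event on the service as a whole, and timing is described for the website but not for the Clinic. Potential Limitations discusses participants who bypass their unique link but does not mention this gap.

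**Conclusion.** The point holds in a limited form. Data Collection and Data Analysis differ on which data define persistence, and the Clinic data named could not date a contact on a Kaplan-Meier curve. If the named sources are followed, persistence with the blended service would be understated, never overstated, through this route.

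The amount depends on how many participants still in TEN are using only the Clinic. Under the assumed 50% true persistence, 5% to 20% Clinic-only lowers the 6-month reading by 2.5 to 10 percentage points. These are illustrations and not estimates for this study. The conclusion assumes that some participants stop visiting the website while in Clinic care and that session dates are not otherwise collected. If either assumption fails, the understatement disappears, though the wording would still need to be aligned.

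**What to change.** 1. In TEN Service Engagement, have clinicians supply the date of each Clinic session as well as access and the count, after checking that participant consent covers this.
2. In Data Analysis, define access to TEN for the Kaplan-Meier curve as either a website access or a Clinic session, and bring the Data Collection sentence into line.
3. Show website-only persistence as a separate, labelled curve, so that the two can be compared.
4. If session dates cannot be obtained, label the curve and the conclusion drawn from it as *website persistence*, and report Clinic access and session counts beside it.

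The cost is one extra data field, a consent check and a few words in three sections. Study 3, Data Collection, says that Clinic service data are routinely captured by clinicians, so the dates may already exist, although the article does not confirm that.
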